## 13. Statistical Analysis

### 13.1 Purpose of Analysis

The purpose of analysis is to evaluate the effect of anticipated therapeutic dose and supratherapeutic dose of TS-071 on QT/QTc interval with QTcF as the primary endpoint and QTcB as the secondary endpoint, and also to confirm the assay sensitivity of the study by employing moxifloxacin (Avelox® tablets) as a positive control.

Another purpose of analysis is to evaluate the safety of anticipated therapeutic dose and supratherapeutic dose of TS-071 with adverse events and adverse drug reactions as evaluation variables.

In addition, the relation of the pharmacokinetics of TS-071 and moxifloxacin to QTc interval will be investigated with plasma concentrations of unchanged TS-071 and unchanged moxifloxacin as evaluation variables.

### 13.2 Analysis Sets

Three kinds of analysis sets are defined: “12-lead ECG analysis set for QT/QTc analysis” for QT/QTc analysis, “Safety analysis set” for safety evaluation and “Pharmacokinetic analysis set” for pharmacokinetic evaluation.

The definition of each analysis set is as follows:

#### (1) 12-lead ECG analysis set for QT/QTc analysis

This analysis set will include all subjects who fulfilled the minimum requirements of the study without any major protocol deviation and for whom 12-lead ECG data for QT/QTc analysis is available. Subjects who are excluded from analysis according to the “Criteria for Handling of Cases and Data” (which will be separately provided) will be excluded from this set.

(2) Safety analysis set

This analysis set will include all subjects who received at least one dose of study drug and for whom safety variable is available. Subjects who are excluded from analysis according to the “Criteria for Handling of Cases and Data” will be excluded from this set.

(3) Pharmacokinetic analysis set

This analysis set will include all subjects who fulfilled the minimum requirements of the study without any major protocol deviation and for whom pharmacokinetic variable is available. Subjects who are excluded from analysis according to the “Criteria for Handling of Cases and Data” will be excluded from this set.

### 13.3 Handling of Cases and Data

#### 13.3.1 Handling of Cases

Handling of cases will be specified in the “Criteria for Handling of Cases and Data”, which will be provided separately.

#### 13.3.2 Handling of Data

Handling of data will be specified in the “Criteria for Handling of Cases and Data”, which will be provided separately. Handling of data for summary/analysis is specified below.

##### 13.3.2.1 Acceptability of Data

The acceptable time windows for each examination are given in “Appendix 3: Acceptable Time Windows for Examinations.” The acceptable range for data will be specified in the “Criteria for Handling of Cases and Data.”

##### 13.3.2.2 Handling of Dates

When a date cannot be identified and documented as beginning, middle, end or unknown period of a month, it will be handled as “5th”, “15th”, “25th” or “15th” of a month, respectively. When a month cannot be identified, it will be handled as “June”, and when a year cannot be identified, it will be handled as “unknown.” When calculating a time period using dates and a negative value of the period is not reasonable but the value is calculated as a negative value, the time period will be handled as “0 day”.

##### 13.3.2.3 Handling of Missing Values

When a data is missing or excluded from analysis, continuous value of such data will be excluded from summary/analysis, and discrete value of such data will be handled as unknown.

##### 13.3.2.4 Handling of Abnormal Data

Abnormality of data will be reviewed before data lock. Abnormal data will be excluded from summary/analysis as abnormal data if the exclusion can be explained reasonably. Abnormality of data will be reviewed from an overall medical point of view.

##### 13.3.2.5 Handling of Values below/above Limit of Quantification

When clinical laboratory values or other laboratory values are below or above limit of quantification, the quantification limit values will be used in summary/analysis for continuous data, and the observed values will be used in summary/analysis for discrete data.

### 13.4 Statistical Analysis Plan

The person responsible for statistical analysis will perform the statistical analysis immediately after data lock based on a statistical analysis plan in accordance with the sponsor's relevant standard operating procedure.

The statistical analysis plan, which will provide further details regarding the contents in this section, will be prepared and fixed prior to the summary/analysis procedure.

When the statistical analysis plan needs to be revised due to a deviation from the original plan or for some other reasons, the person responsible for statistical analysis will create a record specifying the time of amendment, changes made, reason for amendment and the person responsible for amendment in accordance with the sponsor's relevant standard operating procedure.

#### 13.4.1 Significance Level and Confidence Coefficient

The significance level of 5% (two-sided) will be applied in statistical significance testing unless otherwise specified. The confidence coefficient of 95% (two-sided) will be used unless otherwise specified.

#### 13.4.2 Demographics and Other Baseline Characteristics

Regarding subject background characteristics, frequency will be presented for discrete data by treatment sequence, and summary statistics will be provided for continuous data by treatment sequence.

#### 13.4.3 Evaluation Variables and Summary/Analysis Plan

##### 13.4.3.1 Variables for QT/QTc Interval Analysis and Summary/Analysis Plan

<Variables>

QTcF will be the primary endpoint and QTcB will be the secondary endpoint.

<Summary/Analysis plan>

The following analyses will be performed in the 12-lead ECG analysis set for QT/QTc analysis:

(1) Calculation of summary statistics

Summary statistics will be provided for changes from baseline (prior to study drug administration in each study period) in QTc ( $\Delta$ QTc) at each time point after administration and the 95% one-sided confidence intervals will be presented.

(2) Analyses of central tendency

Treatment comparisons between anticipated therapeutic dose or suprathreshold dose (hereinafter referred to as TS-071 groups) and placebo ( $\Delta\Delta$ QTc) will be analyzed using analysis of covariance with  $\Delta$ QTc at each time point as a variable. Least square means and the upper bound of the 95% one-sided confidence intervals of  $\Delta\Delta$ QTc at each time point will be presented. The lower bound of 95% one-sided confidence interval will be presented similarly for Avelox treatment.

The effect of TS-071 on QT/QTc interval prolongation will be regarded negative when the upper

bound of the 95% one-sided confidence interval for the mean effect on the QT/QTc interval excludes 10 msec at all the time points in the TS-071 groups. The assay sensitivity will be regarded as established when the lower bound of the above-described 95% one-sided confidence interval excludes 0 msec at any of the time points in the Avelox treatment.

(3) Categorical analyses

The number and percentage of subjects whose QTc value after study drug administration exceeded 450 msec, 480 msec or 500 msec will be calculated by treatment group. The number and percentage of subjects whose  $\Delta$ QTc value exceeded 30 msec or 60 msec by treatment group.

(4) Graphical presentation

Scatter plots of QTc and RR will be presented by treatment group to verify the validity of QT corrections. Scatter plots of  $\Delta\Delta$ QTcF and plasma concentrations will be presented for TS-071 groups and Avelox treatment to investigate the relationship between  $\Delta\Delta$ QTcF and plasma concentrations.

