## 10.8 Evaluation of 12-Lead ECG Data for QT/QTc Analysis

12-lead ECG for QT/QTc analysis will be recorded according to a separate written procedure and recordings will be read at the central ECG analysis facility. The same model of 12-lead digital surface ECG monitor should be employed for all the subjects at all the time points.

Three charts of 12-lead ECG for QT/QTc analysis will be recorded in 5 min for each time point as shown in

“Table 10-2 Time Points for 12-Lead ECG for QT/QTc Analysis.” The interval between the start of each recording should be  $\geq 1$  min, and ECG will be recorded for 10 seconds for each chart. The acceptable time windows for recording ECG are given in “Appendix 3: Acceptable Time Windows for Examinations.” All 12-lead ECG charts for QT/QTc analysis will be sent electronically by the responsible person of the study site to the central ECG analysis facility. The time of recording 12-lead ECG for QT/QTc analysis (3 charts to be measured by the central ECG analysis facility) will be documented in the CRF. For the time points when 12-lead ECG are recorded for safety evaluation only, the time of recording 12-lead ECG for safety evaluation except post-treatment examination will be documented in the CRF.

For all the ECG charts for QT/QTc analysis sent to the central ECG analysis facility, RR, QT, PR and QRS intervals will be measured in accordance with the procedure of the facility. The time of recording and subject identification information should be shielded before measurement. QTc intervals will be corrected by Fridericia’s and Bazett’s formulae.

The effect of TS-071 on QT/QTc interval prolongation will be regarded negative when the upper bound of the 95% one-sided confidence interval for the largest mean effect on the QT/QTc interval excludes 10 msec at all the time points in the TS-071 groups.

In addition, pharmacokinetic parameters will be determined from plasma concentrations of unchanged TS-071 and moxifloxacin, and an exploratory investigation will be made to assess the relationship of drug concentrations to changes in QT/QTc interval.

Table 10-2 Time Points for 12-Lead ECG for QT/QTc Analysis

| Variable                         | Time after study drug administration                                     |
|----------------------------------|--------------------------------------------------------------------------|

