| 12-lead ECG for QT/QTc analysis* | Pre-dose and 0.5, 1, 2, 3, 4, 6, 8, 24 hr post-dose in each study period |

\*: 12-lead ECG will be recorded in the supine position after resting for 10 min.

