### 13.4.4 Statistical Interpretation of Analysis Results

Effects on QT/QTc prolongation in the TS-071 groups and assay sensitivity of the study will be interpreted as

described in “13.4.3.1 Variables for QT/QTc Interval Analysis and Summary/Analysis Plan.”

Clinical interpretation of the analysis results will be evaluated comprehensively by reviewing all the variables and described in the clinical study report.

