#### 13.4.5 Multiplicity Adjustment

The effect of TS-071 on QT/QTc interval prolongation will be regarded negative when the upper bound of the 95% one-sided confidence interval for the mean effect on the QT/QTc interval excludes 10 msec at all the time points in the TS-071 groups. There is no need for multiplicity adjustment because alternative hypothesis is expressed as an intersection of alternative hypothesis at each time point.

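### Assay sensitivity can be declared on any one of eight unadjusted Avelox tests, and the negative TS-071 conclusion does not depend on it

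*Protocol*

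**What the plan says.** Section 13.4.3.1, under analyses of central tendency, sets two decision rules in consecutive sentences.

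- **TS-071:** a negative result requires this of the upper limit in both dose groups: "bound of the 95% one-sided confidence interval for the mean effect on the QT/QTc interval excludes 10 msec at all the time points".
- **Avelox:** assay sensitivity is established when the "lower bound of the above-described 95% one-sided confidence interval excludes 0 msec at any of the time points in the Avelox treatment".

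The Avelox bound is set at the same level as the TS-071 bound: "The lower bound of 95% one-sided confidence interval will be presented similarly for Avelox treatment". Table 10-2 in section 10.8 gives the ECG times as "Pre-dose and 0.5, 1, 2, 3, 4, 6, 8, 24 hr post-dose in each study period", which is eight post-dose times.

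The only multiplicity provision is in section 13.4.5. It restates the TS-071 rule and then says: "There is no need for multiplicity adjustment because alternative hypothesis is expressed as an intersection of alternative hypothesis at each time point".

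Section 13.1 gives the role of the positive control as "to confirm the assay sensitivity of the study by employing moxifloxacin". Section 13.4.4 names the TS-071 effect and assay sensitivity together and refers back to section 13.4.3.1. It does not make one depend on the other.

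**The concern.** The two rules point in opposite directions. TS-071 must pass at every time point, so testing at more times makes success harder and no adjustment is needed. Avelox has to pass only once, so each extra time point is another chance to succeed. With all in one sentence and any in the next, any can only mean at least one. The justification in section 13.4.5 does not reach a rule of that kind, and no adjustment, named window or ordering is given for it. A single positive bound at 0.5 h or 24 h would satisfy the rule, although section 9.1.3 gives a mean moxifloxacin Tmax of 1.75 h.

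The second gap concerns how the two results are combined. The negative rule appears in sections 10.8, 13.4.3.1 and 13.4.5, and in none of them is it conditional on assay sensitivity. Read literally, TS-071 can be called negative in a trial whose positive control failed.

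Both gaps bear on how a negative result can be read. The sample size of 56 rests on reference to overseas studies (section 9.3), with no SD, effect size or power stated. The Avelox check is therefore the main safeguard against reading an insensitive trial as a negative one.

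**Working it through.** The protocol states no overall error rate for the Avelox rule, so there is no figure to reproduce.

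**Inputs from the protocol:** m = 8 post-dose times (Table 10-2); one-sided 5% at each (section 13.4.3.1); pass if at least one lower bound exceeds 0 msec; n = 56 (section 9.3).

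**Assumptions:** no Avelox effect over placebo at any of the eight times; normal test statistics; and a correlation between time points, which the protocol does not give.

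**False-pass rate, independent times.** 1 − 0.95^8 = 0.337.

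**False-pass rate, equal correlation ρ.** 1 − ∫ φ(x) · Φ((1.645 − √ρ·x)/√(1−ρ))^8 dx:

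| ρ | False-pass rate |
|---|---|
| 0 | 33.7% |
| 0.3 | 26.7% |
| 0.5 | 21.9% |
| 0.7 | 16.8% |
| 0.8 | 14.1% |
| 0.9 | 10.9% |

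A first-order autoregressive pattern (1,000,000 simulated draws) gives 27.5% at 0.5, 22.5% at 0.7 and 14.4% at 0.9. The rate exceeds 5% at every correlation below 1.

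All times in a period share one pre-dose baseline, so independence is an upper-end case. Plain change scores with equal, independent errors would give ρ = 0.5. The plan uses an analysis of covariance whose covariates section 13.4.3.1 does not name, so 0.5 cannot be derived for it.

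**Effect of naming times without adjusting.** Four named times at one-sided 5% each: 1 − 0.95^4 = 18.5% at ρ = 0, and 12.0% at ρ = 0.7. Naming a window alone is not enough.

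**Effect of Bonferroni at ρ = 0.**
- Four times at 0.05/4 = 1.25% each: 1 − 0.9875^4 = 4.9%.
- Eight times at 0.05/8 = 0.625% each: 1 − 0.99375^8 = 4.9%.

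Both rates fall as ρ rises. The eight-time version gives 3.8% at 0.5 and 2.9% at 0.7.

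**Price of adjusting.** The normal quantile rises from 1.645 to 2.241 (four times) or 2.498 (eight times). With an assumed SD of the paired difference of 10 to 12 msec, the SE is SD/√56 = 1.3 to 1.6 msec.
- Four times: the lower bound drops by (2.241 − 1.645) × SE = 0.8 to 1.0 msec.
- Eight times: it drops by (2.498 − 1.645) × SE = 1.1 to 1.4 msec.

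Single-time-point power is 1 − Φ(z − effect/SE). All effects and SDs here are assumed:

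| Effect, SD (msec) | Unadjusted | Bonferroni, 4 times | Bonferroni, 8 times |
|---|---|---|---|
| 8, 12 | 99.96% | 99.7% | 99.4% |
| 5, 15 | 80% | 60% | 50% |

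For the second row, SE = 15/√56 = 2.00 and 5/2.00 = 2.49. Power is then Φ(2.49 − 1.645) = 80%, Φ(2.49 − 2.241) = 60% and Φ(2.49 − 2.498) = 50%.

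**The case against.** Several points on the other side are fair.

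- **The false-pass rates assume no Avelox effect at all.** Section 9.1.1 describes moxifloxacin as a known QT prolonger. The percentages are error rates under that null. A reader might take them as the chance that this trial will mislead, and the documents do not support that.
- **The size depends on correlation.** A reader might quote 34% as the answer, but it needs independent time points, which a shared baseline makes unlikely. The high-correlation end, 11% to 14%, belongs in the range.
- **Section 13.4.5 does not claim to cover Avelox.** It names only TS-071 and is right about TS-071. A reader might infer that the section misapplies its argument or that the TS-071 test is invalid. Neither follows: the fault is silence on a rule that needs control.
- **The two results are not treated as unrelated.** They stand side by side in section 13.4.3.1. Section 13.4.4 interprets both and calls for a comprehensive clinical interpretation. The Avelox bound is shown at each time point and plotted against concentration, so a lone pass at 0.5 h or 24 h would be visible. Visibility helps a careful reader but does not change the pre-specified rule.
- **A separate analysis plan may add detail.** Section 13.4 provides for one and it is not at hand. However, the protocol does not leave this open: it fixes the unadjusted any-time rule and an unconditional negative rule, and a plan that adjusted would depart from it.

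These points narrow the size and the wording. They do not remove either gap.

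**Conclusion.** The Avelox rule is wrong as written. It permits eight unadjusted one-sided 5% tests, one success is enough, and nothing in the protocol controls the resulting error. With no Avelox effect at any time, the false-pass rate is about 11% to 34% for an assumed equal correlation from 0.9 down to 0, and 22% at 0.5. The direction does not depend on that assumption, but the size does.

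Separately, a negative TS-071 conclusion is not conditional on assay sensitivity in any of the places where the rule is stated, although section 13.1 makes confirming it a purpose of the analysis. The all-time-points rule for TS-071 remains valid without adjustment. What is weakened is the check that makes a negative result credible.

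**What to change.** 1. In section 13.4.3.1, pre-specify a procedure for Avelox that holds the familywise one-sided error at 5%. One option is a few named times around the documented Tmax, for example 1, 2, 3 and 4 h at one-sided 1.25% each under Bonferroni. The other is all eight times at 0.625% each. Either Bonferroni version keeps the false-pass rate at or below 5%. Hochberg is less conservative, though its guarantee relies on non-negative dependence between time points. The 1 to 4 h window is one reasonable choice, not the only one.
2. In section 13.4.5, add the Avelox procedure alongside the TS-071 argument.
3. In sections 13.4.3.1 and 13.4.5, state that TS-071 is concluded negative on QTcF only if assay sensitivity is established, and align section 10.8 and synopsis section 5.2.

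No extra data are needed, but section 14.2 requires agreement with the investigator and IRB approval for a protocol amendment. The statistical price is the lower Avelox bound and the loss of power shown above. It is negligible if the effect is large relative to its SE, and material if the effect is small and the data noisy. The sponsor should therefore state the SD and effect it expects before choosing between four and eight times.

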### 13.4.3.2 Analysis Plan for Safety Variables

<Variables>

- (1) Adverse events and adverse drug reactions, including abnormal changes in body temperature, blood pressure, pulse rate, 12-lead ECG and clinical laboratory tests
- (2) Effects on body temperature, blood pressure, pulse rate, 12-lead ECG and clinical laboratory tests

<Summary/Analysis plan>

Following analyses will be performed in the safety analysis set:

Frequency of adverse events and adverse drug reactions based on each symptom and finding will be presented. Number of adverse events and adverse drug reactions will be summarized by relationship to study drug and also by relationship to study drug (“Not related” and other than “Not related”) and severity.

The incidence (%) of adverse events and adverse drug reactions will be calculated. Summary statistics will be provided for body temperature, blood pressure, pulse rate and clinical laboratory tests at each time point, and changes from baseline (prior to study drug administration in each study period) will also be summarized by summary statistics.

### 13.4.3.3 Analysis Plan for Pharmacokinetic Variables

<Variables>

Plasma concentrations of unchanged TS-071 and its metabolites (M-2 and M-17), and unchanged moxifloxacin

<Summary/Analysis plan>

Pharmacokinetic parameters including Cmax, Tmax, AUC and T1/2 of the pharmacokinetic variables will be determined by noncompartment analysis in the pharmacokinetic analysis set.

### 13.4.4 Statistical Interpretation of Analysis Results

Effects on QT/QTc prolongation in the TS-071 groups and assay sensitivity of the study will be interpreted as

described in “13.4.3.1 Variables for QT/QTc Interval Analysis and Summary/Analysis Plan.”

Clinical interpretation of the analysis results will be evaluated comprehensively by reviewing all the variables and described in the clinical study report.

#### 13.4.5 Multiplicity Adjustment

The effect of TS-071 on QT/QTc interval prolongation will be regarded negative when the upper bound of the 95% one-sided confidence interval for the mean effect on the QT/QTc interval excludes 10 msec at all the time points in the TS-071 groups. There is no need for multiplicity adjustment because alternative hypothesis is expressed as an intersection of alternative hypothesis at each time point.

#### 13.4.6 Interim Analysis

No interim analyses will be performed in this study.

### 13.5 Finalization of Criteria for Handling of Cases and Data

The “Criteria for Handling of Cases and Data” will be finalized prior to data lock. For finalizing the criteria, the handling of each data and case as well as the handling of problematic cases which were not stipulated when planning the protocol will be reviewed upon consulting with the medical expert where necessary.

When any of the handling criteria is changed, it should be described in detail in the clinical study report including the time of change, details of amendments and the reason.

### 13.6 Finalization of Statistical Analysis Plan

The statistical analysis plan will be finalized after the sponsor reviews the appropriateness of the summary/analysis methods and necessity to define the handling of data to be analyzed by the methods other than those described in the statistical analysis section of the protocol.

When the statistical analysis plan is revised, it should be documented by specifying the time of amendment, details of amendments, reason and the person responsible for amendment. The amendment will also be described in the clinical study report.

## 14. Protocol Compliance, Deviations or Changes and Amendments

### 14.1 Protocol Compliance and Deviations or Changes

The principal investigator or subinvestigator should not deviate from or change the protocol without prior written agreement between the principal investigator and the sponsor and without prior review and written approval of the IRB except where necessary to eliminate an immediate hazard to subjects or for clerical changes such as a change of phone number.

- (1) The principal investigator or subinvestigator may deviate from or change the protocol to eliminate an immediate hazard to study subjects without prior written agreement between the principal investigator and the sponsor and without prior written approval of the IRB. In this regard, the principal investigator will notify the sponsor of the deviation or change together with its reason, and discuss and agree the proposed protocol amendment with the sponsor. A draft protocol amendment

should be reviewed and approved by the IRB via the head of the study site without delay.

- (2) The investigator must immediately report to the IRB via the sponsor and the head of the study site every change in the protocol that will have significant impact on the conduct of the study or increase the hazard to subjects.
- (3) The principal investigator or subinvestigator will record all actions deviated from the protocol. As to protocol deviations to eliminate an immediate hazard to study subjects or for other medically compelling reasons, the principal investigator will immediately provide the sponsor and the head of the study site with a document explaining the reason and retain the copy thereof.

